## Abstract

**Background:**

Radiotherapy is one of the cornerstones of the treatment of Head and Neck Squamous Cell Carcinomas *(*HNSCC). However, radioresistance is associated with a high risk of recurrence. To propose strategies (such as combinations with drugs) that could over intrinsic radioresistance, it is crucial to predict the response to treatment. Patient-Derived Tumor Organoids (PDTO) are in vitro tridimensional microtumors obtained from patient’ own cancer samples. They have been shown to serve as reliable surrogates of the tumor response in patients.

**Methods:**

The ORGAVADS study is a multicenter observational trial conducted to investigate the feasibility of generating and testing PDTO derived from HNSCC for the evaluation of sensitivity to treatments. PDTO are obtained after dissociation of resected tumors remaining from tissues necessary for the diagnosis. Embedding of tumor cells is then performed in extracellular matrix and culture in medium supplemented with growth factors and inhibitors. Histological and immunohistochemical characterizations are performed to validate the resemblance between PDTO and their original tumor. Response of PDTO to chemotherapy, radiotherapy and innovating combinations are assessed, as well as response to immunotherapy using co-cultures of PDTO with autologous immune cells collected from patient blood samples. Transcriptomic and genetic analyses of PDTO allow validation of the models compared to patients’ own tumor and identification of potential predictive biomarkers.

**Discussion:**

This study is designed to develop PDTO models from HNSCC. It will allow comparing the response of PDTO to treatment and the clinical response of the patients from whom they are derived. Our aim is to study the PDTO ability to predict the clinical response to treatment for each patient in view of a personalized medicine as well as to establish a collection of HNSCC models that will be useful for future innovative strategies evaluation.

**Trial registration:**

NCT04261192, registered February 7, 2020, last amendment v4 accepted on June, 2021.

## Background

### Head and neck squamous cell carcinoma (HNSCC) and treatment modalities

HNSCC is the sixth most common cancer worldwide, with 890,000 new cases and 450,000 deaths in 2018 [1]. It is estimated that locoregional control can be achieved in half of the cases, in part because 65% of patients are diagnosed at advanced stages (T3T4) and also because locoregional relapse is frequent. The prognosis of HNSCC is poor with a 5-year survival rate for all stages around 55% [1].

Treatment of HNSCC is based on several modalities. Surgery is chosen when a total excision is possible. Radiotherapy may be proposed as primary treatment or as adjuvant treatment depending on the existence of poor prognostic factors (margin status, capsular rupture, advanced tumors, etc.) [2]. Systemic treatments such as chemotherapy (cisplatin) or targeted therapy (cetuximab) can be used in combination with radiotherapy. At the recurrent or metastatic phase, HNSCC are often treated with systemic treatments. Immunotherapy has also entered the therapeutic arsenal for HNSCC with the use of anti-PD1 (programmed death-1) agents Nivolumab or Pembrolizumab [1].

The prognosis of HNSCC is burdened by radioresistance, which is partly due to hypoxia and proliferation among other reasons. This explains the lack of effectiveness of radiotherapy in many cases. Research is thus focused on mechanisms factors of radioresistance. Among them, genomic instability of DNA repair systems plays an important role [3]. Molecules affecting DNA repair systems are currently being studied such as PARP inhibitors like Olaparib which was FDA-approved in 2014 since they could allow sensitization of tumor cells to radiotherapy [4]. Another promising field of research is the use of different particles such as proton beam therapy. It has two major advantages over X-rays: more precise energy delivery to the tumor and fewer side effects on surrounding healthy tissues [5].

Patients with HNSCC suffer from numerous complications of treatment. The side effects are increased by therapeutic combinations. These treatments can alter breathing, phonation and swallowing because of the tissue changes caused by the radiation in the areas surrounding the tumor. Patients’ quality of life is altered by functional disorders and by the social impact of treatments. Predicting tumor response and tissue effects from innovative combinations has the potential to improve the therapeutic index.

### Toward predictive medicine

Precision medicine is an innovative approach to tailoring disease treatment that takes into account differences in genetics, environment, and lifestyle of people. The goal of precision medicine is to target treatments to patients who are most likely to benefit from them. Due to the specific problems of HNSCC (radioresistance, high risk of recurrence and secondary cancer, toxicity of treatments), it appears interesting to be able to predict response to conventional treatments using models mimicking the original patient’s tumor. Such models could also be used to test new therapy combinations or new compounds in order to predict their clinical effectiveness and/or the identification of predictive molecular signatures.

Functional assays in precision oncology are based on direct exposure of cancer tissues derived from affected individuals to drugs to predict clinical response. These functional approaches allow to evaluate the response to treatments by considering all the intrinsic characteristics of the tumor without prior molecular analysis. The results can then be correlated to different biological parameters (DNA, mRNA, non-coding RNA, proteins, etc. from various origins like tumor or blood for example) in order to identify predictive biomarkers of treatment response. Functional assays can be performed using various cancer models [6], including Patient-Derived Tumor Organoids (PDTO) which represent an emerging pre-clinical model at the interface of cell lines and patient-derived xenografts mouse models.

PDTO are obtained after dissociation of tumor samples and embedding of tumor cells in extracellular matrix. They are cultured in medium containing a cocktail of growth factors and signaling pathway inhibitors. These culture conditions have been successfully used to establish long-term PDTO lines from many types of cancers [7]. The feasibility of generating HNSCC organoid lines has previously been shown since PDTO from squamous cell carcinoma of the oral cavity [8] and oropharynx [9] have been established in the last few years. These PDTO have the advantages of being able to be amplified relatively quickly after tumor resection, having unlimited potential for proliferation, a high rate of successful establishment, and the ability to be transfected and cryopreserved [10]. These characteristics allow them to recapitulate the cancer spectrum [11]. Moreover, they are close to the original tumor in terms of histological and molecular features [11, 12].

### PDTO could predict the response of the tumor

More and more evidence indicate that PDTO may predict the response of the tumor from which they are derived [7]. A pilot study showed that PDTO from metastatic gastrointestinal tumors predicted the response of 21 patients to different chemotherapies (100% sensitivity, 93% specificity, 88% positive predictive value and 100% negative predictive value) [13]. Another study using PDTO from 11 chemo-naive pancreatic tumors gave a 91% predictive response rate to first-line chemotherapy and 80% to second line chemotherapy [14].

The predictive value of tumor PDTO is also observed for radiotherapy. In their study analyzing 19 patients suffering from colorectal cancer, Park et al. were able to develop a model to predict radio-sensitivity (82% accuracy) and radioresistance (93% accuracy) of patients [15]. Moreover, Driehuis et al. showed that PDTO derived from patients with the worst progression-free survival for HNSCC were more likely to be resistant to radiotherapy [8]. Finally, the response to a combination of chemotherapy and radiotherapy could be efficiently predicted (84% accuracy) using PDTO from colorectal cancer [16]. Altogether, these data highlight the predictive value of PDTO and the relevance to use them to anticipate the response to radiotherapy and its combinations with other treatments. Since the tumor microenvironment also play a critical role in dictating the response to therapies, more and more work is done to complexify the culture of PDTO in order to faithfully recapitulate it. Several trials to culture PDTO with fibroblasts, macrophages or T cells have thus been conducted [17] and gave rise to complex in vitro models. Some of them were used to evaluate the response to immunotherapy in PDTOs derived from melanoma [18] or appendicular cancers [19] and displayed a promising correlation with the clinical response (85 and 100% accuracy respectively). More evidence is still needed to conclude and several trials are currently running to evaluate the predictive value of PDTO in a clinical context [6].

If the predictive value of PDTO model is validated, this would allow testing conventional treatments before administering them to the patient from whom the PDTO are derived. This perspective is very interesting, particularly in HNSCC where more than two thirds of the operated patients will undergo adjuvant treatments such as radiotherapy and/or chemotherapy whose side effects can be important. Despite these treatments, up to half of patients will relapse, highlighting the radio-chemosensitivity heterogeneity of tumors [20]. A predictive screening using PDTO could thus help to refine the choice of treatments adapted to each patient and thus limit adverse effects. As immunotherapies are increasingly considered to treat HNSCC, the development of PDTO models capable to i) assess the efficacy of such treatment and ii) predict patients’ response to these new agents; will be critical in the next few years. In this regard, our study will allow a first set of functional assays in PDTO co-cultured with autologous immune cells and will give initial pieces of evidence about the efficacy of immunotherapies in HNSCC.

## Methods/design

The ORGAVADS study is a multicenter observational study conducted to investigate the feasibility of generating and testing PDTO from HNSCC for evaluation of sensitivity to treatments (Fig. 1). The ORGAVADS study and this manuscript have been written in accordance with standard protocol items, namely recommendations for interventional trials (SPIRIT).

**Fig. 1 Fig1:**
[figure not shown]
ORGAVADS study design

### Study objectives

The main objective of the study is to assess the feasibility of using PDTO from HNSCC as tools for predicting response to treatments.

The secondary objectives are: i) to assess the feasibility of in vitro functional assays for evaluation of sensitivity to treatments (chemotherapy, radiotherapy, PARP inhibitors and immunotherapy); ii) to investigate the predictive value of PDTO for conventional chemotherapy and radiotherapy; iii) to evaluate the PARP inhibitor-mediated sensitization of radiotherapy; iv) to assess the ability of PDTO to repair DNA lesions by homologous recombination [(HRD (Homologous Recombination Deficiency)/HRI (Homologous Recombination Intermediate)/HRP (Homologous Recombination Proficiency) status); v) to identify molecular signatures for prediction of response (of PDTO and patients) to treatments.

### Study population

Eligibility criteria are described in Table 1. The ORGAVADS study focuses on patients with surgically resectable HNSCC who undergo surgery at François Baclesse Center and Caen University Hospital Center. After patient screening according to criteria, and the patient’s non-opposition, the patient will be enrolled in the study. An identification number will be thus assigned to each patient to be used throughout the study.

**Table 1 Tab1:** ORGAVADS study inclusion and exclusion criteria

Inclusion criteria	Non-inclusion criteria
Patient ≥ 18 years	Pregnant women
Histologically confirmed squamous cell carcinoma of the oral cavity, oropharynx, hypopharynx or larynx	Patient deprived of liberty or placed under the authority of a tutor
Patients for whom oncologic surgery is planned or who have recently undergone surgery of the tumor of oral cavity, oropharynx, hypopharynx or larynx	
Subject affiliated to a social security regimen	
No opposition to participate to the study	

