#### Medical data collection

Medical data collected for each patient in order to correlate biological data (including PDTO response to treatment) with clinical response are indicated in Table 2.

**Table 2 Tab2:** Medical data collected for each patient

Clinical parameters	Age, sex, weight, height, ECOG performance status, Exposure to tobacco and alcohol, Cancer location and TNM-8 classification
Histological diagnosis	Type, squamous differentiation, keratinization type, p16 status
Biologic parameters	Serum neutrophils, albumin and leukocytes levels
Pathological pronostic factors	Surgical margin, lymph node metastasis with or without capsular rupture, vascular or lymphatic embolization, perineural invasion
Oncologic treatments	Radiotherapy (volume, dose, fraction) Chemotherapy (molecules, administration regimen)
Response to treatment	Disease-free survival, Progression-free survival, Overall survival.

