#### Evaluation of response to treatments

The evaluation of the response to treatments will be performed when PDTO have reached a diameter of 150 μm in « PDTO treatment medium », corresponding to the PDTO culture medium lacking N-Acetylcysteine, Y-27632 and primocin.

PDTO will be collected, resuspended in 2% extracellular matrix/PDTO culture medium and then platted in white and clear bottom 96-well plates previously coated with a 1:1 volume mix of PDTO treatment medium with extracellular matrix. In the case of evaluation of the response to radiotherapy, PDTO will be before irradiated using the CellRad System (FAXITRON Bioptics). In the case of evaluation of the response to chemotherapy or PARP inhibitors, drugs are prepared in 2% extracellular matrix/PDTO culture medium and added 1 hour after PDTO have been plated.

In the case of evaluation of the response to immunotherapies, PDTO will be co-cultured with PDTO specific T cells previously generated (*see co-culture of PDTO with immune cells*) at a 5:1 ratio. Treatments (such as Nivolumab or Pembrolizumab) will be added directly in the co-culture. A condition containing an MHC-I blocking antibody will be added to control for antigen specific killing.

PDTO morphology will be monitored by taking images during the required time using Incucyte S3 (Sartorius). At the endpoint, PDTO response will be assessed using CellTiter-Glo 3D cell viability assay (Promega) according to the manufacturer’s instruction and luminescence will be measured using GloMax Discover GM3000 (Promega) with the associated software. Results will be normalized to the control condition. IC50 will be calculated with GraphPad software. The ability of T cells to recognize and induce lysis of PDTO will be monitored via analysis of caspase 3 cleavage within PDTO and visualization of LAMP-1 on the membrane of CD8+ T cells.

The treatment response of the PDTO will be finally compared to the clinical response (PFS/DFS/OS) of the patient from whom they are derived in order to validate the predictive value of this model for HNSCC.

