#### Statistical analyses

Qualitative variables will be described using the sample numbers and percentages. Quantitative variables will be described using the mean (+/− standard deviation) or the median and the range if normality hypothesis is not verified*.*

To address the primary objective, the rate of successful PDTO establishment, i.e., the rate of tumor samples usable for predictive functional assays based on PDTO, will be estimated with its 95% confidence interval. Then, PDTO response to treatment will be correlated with the clinical response by performing a Chi2 test and computing the Cohen’s kappa coefficient. Associations between biological parameters and clinical response will be assessed by one-way analysis of variance (or the non-parametric Kruskal-Wallis test, if necessary). Receiver Operating Characteristic (ROC) curves and a logistic regression model will also be used to identify predictive factors of clinical response.

An alpha level of 5% will be considered to indicate statistical significance for each statistical analysis and confidence interval.

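### In a resected cohort, Cohen's kappa between organoid response and DFS/PFS/OS understates the assay, so it cannot on its own validate treatment-specific predictive value

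*Protocol article*

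**What the plan says.** All references are to the Protocol article.

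- **Who is enrolled.** Study population: "The ORGAVADS study focuses on patients with surgically resectable HNSCC who undergo surgery". The surgical criterion in Table 1 is "Patients for whom oncologic surgery is planned or who have recently undergone surgery of the tumor". It does not require complete excision, residual disease or adjuvant treatment.
- **When surgery is used.** The background section on treatment modalities says: "Surgery is chosen when a total excision is possible". It adds that radiotherapy may follow as adjuvant treatment when poor prognostic factors are present.
- **What happens after surgery.** The background section on PDTO as predictors says "more than two thirds of the operated patients will undergo adjuvant treatments such as radiotherapy and/or chemotherapy", and then "Despite these treatments, up to half of patients will relapse".
- **What counts as clinical response.** Table 2 lists only DFS, PFS and OS under response to treatment. It also records the treatments given and the pathological factors: "Surgical margin, lymph node metastasis with or without capsular rupture, vascular or lymphatic embolization, perineural invasion".
- **What is done with them.** Evaluation of response to treatments compares organoid response with PFS/DFS/OS "in order to validate the predictive value of this model for HNSCC". Statistical analyses gives the method: "PDTO response to treatment will be correlated with the clinical response by performing a Chi2 test and computing the Cohen’s kappa coefficient". ROC curves and logistic regression are also planned.

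Predictive value for chemotherapy and radiotherapy is secondary objective ii. The primary analysis is the establishment rate.

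**The concern.** Kappa treats two classifications as readings of the same quantity. Here they are not. The organoid assay reads the intrinsic sensitivity of the resected tumour. Survival without disease after resection depends first on whether viable tumour was left behind, and only then on whether adjuvant treatment controlled it. If surgery cleared the disease, a resistant organoid is a correct result that the table counts as an error. If the patient received no adjuvant treatment, there is no response to predict at all.

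At stake is the reading of secondary objective ii. A low or moderate kappa could reflect a poor assay, or a good assay in a cohort where surgery did much of the work, and the coefficient cannot tell these apart.

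**Working it through.** **1. The plan's own figure.** No figure is given for the kappa analysis. The only sample size is for the establishment rate: 60%, 95% CI of width 20%, n = 89. The Wilson width is 2z√[p(1−p)/n + z²/(4n²)] / (1 + z²/n). With p = 0.60, n = 89 and z = 1.96 it is 0.1995, so 89 reproduces. The 98 follows from 89 × 1.1 = 97.9. Nothing below affects this.

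**2. Model for the best case.** Among treated patients let q be the share with resistant organoids and c the share already cleared by surgery, taken as independent of the assay result. The document does not give c, so it is varied. Assume a perfect assay: sensitive tumours never relapse, and resistant ones relapse only if disease remains. Then:

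- relapse R = q(1−c)
- sensitive and no relapse: 1−q; sensitive and relapse: 0
- resistant and no relapse: qc; resistant and relapse: q(1−c)
- observed agreement Po = 1−qc
- chance agreement Pe = (1−q)(1−R) + qR
- kappa = (Po−Pe)/(1−Pe)

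**3. Anchored to the document's relapse figure.** The article says up to half relapse despite treatment, so take R = 0.50 as the upper value. Then Pe = 0.50 and kappa = 1−2qc, with q = 0.50/(1−c):

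- c = 0.10: q = 0.556, Po = 0.944, kappa = 0.89
- c = 0.20: q = 0.625, Po = 0.875, kappa = 0.75
- c = 0.30: q = 0.714, Po = 0.786, kappa = 0.57
- c = 0.40: q = 0.833, Po = 0.667, kappa = 0.33

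As c nears 0.50, kappa nears 0. Lower relapse rates give higher caps:

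| c | R = 50% | R = 40% | R = 25% |
|---|---|---|---|
| 0.20 | 0.75 | 0.80 | 0.85 |
| 0.30 | 0.57 | 0.67 | 0.75 |
| 0.40 | 0.33 | 0.50 | 0.64 |
| 0.50 | near 0 | 0.29 | 0.50 |

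**4. The direction is not special to a perfect assay.** Let pA be the share called resistant, pT the share truly resistant, and cov the covariance of the two. Kappa against true resistance is 2cov/(pA + pT − 2pA·pT). If relapse is true resistance thinned by the independent factor (1−c), kappa against relapse is 2cov/(pA/(1−c) + pT − 2pA·pT). The denominator is larger for any c above 0, so any assay better than chance is understated.

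**5. Including patients without adjuvant treatment.** Let t = 2/3 be treated, and suppose relapse in the rest is unrelated to the assay. With q = 0.5, Pe = 0.5 and Po = t(1−0.5c) + (1−t)·0.5, so kappa = t(1−c). For c = 0.2, 0.3, 0.4 and 0.5 this is 0.53, 0.47, 0.40 and 0.33. Treated patients alone would give 1−c, that is 0.80, 0.70, 0.60 and 0.50.

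**6. Is an association still detectable?** Expected lines from treated patients are about 89 × 0.60 × 2/3 = 35.6, say 36. In 20,000 simulated tables of 36 patients with a perfect assay, Chi2 at 5% has power of about 88% at R = 50%, c = 0.40, and over 99% in the other scenarios run. In the same simulations kappa is itself imprecise: its 2.5th to 97.5th percentiles are 0.33 to 0.82 at R = 50%, c = 0.30, and 0.12 to 0.58 at c = 0.40.

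**The case against.** The strongest reply is that the size of the problem rests on a clearance share that appears nowhere in the document, and that the text points towards substantial residual disease. Adjuvant radiotherapy is tied to poor prognostic factors such as margins and capsular rupture, so treated patients are selected for residual risk. Up to half relapse, and margin status is collected because incomplete clearance is anticipated. With 10% or 20% clearance the cap is 0.89 or 0.75, which is not poor agreement. This stands: the effect may be small or large.

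Second, kappa is not the only analysis. Chi2, ROC curves and logistic regression are planned, and no kappa threshold or decision rule is set. This also stands, with a limit: those analyses use the same mixed outcome. They can show association, but cannot by themselves separate treatment response from surgical clearance.

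Third, restriction to patients who received the tested treatment may be spelled out in the full protocol, which an article condenses. That may be so, and the treatments given are collected. But restriction removes only the dilution in step 5; the caps in step 3 already apply to treated patients alone.

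Fourth, the objective is secondary and worded as an investigation. True, but the article elsewhere says that the comparison is made to validate the model, and that is the wording at issue.

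**Conclusion.** The point holds for the kappa analysis and the validation wording. In this cohort DFS/PFS/OS combine surgical clearance with adjuvant response, so kappa falls below the assay's true accuracy. Under a perfect assay and 50% relapse, the maximum is about 0.89 to 0.33 for clearance shares of 10% to 40%. This rests on three assumptions: clearance is independent of the assay result, relapse occurs only with residual resistant disease, and clearance lies within the range shown. Kappa alone therefore cannot validate treatment-specific predictive value under secondary objective ii.

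A reader might go further and infer that every patient was completely excised, that even a perfect assay would agree poorly, and that the plan would wrongly find organoids non-predictive. The document does not support this. Complete excision is not an eligibility criterion, and the statement on total excision is background. The clearance share is unknown, and at 50% relapse the cap falls to about 0.33 only once clearance reaches about 40%. Association would remain detectable if the assay is good. The primary objective and its sample size are unaffected.

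**What to change.** **Statistical analyses.**

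- Limit the comparison of organoid response with outcome to patients who received the matching adjuvant treatment.
- Report recurrence in patients with resistant and with sensitive organoids, and the difference with its 95% CI.
- Stratify by, or adjust for, the margin status and capsular rupture already collected. With about 36 patients and at most about 36 × 0.50 = 18 recurrences, there is room for little more than these two factors.
- Keep kappa, if at all, as a descriptive figure shown beside its attainable maximum. In the model above, this follows from the observed shares of resistant organoids (q) and of relapse (R): (1−(q−R)−Pe)/(1−Pe).

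**Evaluation of response to treatments.** Replace the claim of validating predictive value with association between organoid response and recurrence after surgery plus adjuvant treatment.

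**Cost.** This changes analysis and wording only, with no extra patients, procedures or data fields. The price is a more modest claim and a smaller analysed subset.
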